### Intervention

#### Background

Our self-help intervention is based on Cognitive Behavioural Therapy (CBT). CBT nowadays is a widely used and extensively researched treatment. The effectiveness is supported by numerous studies for many mental disorders [32]. In addition to CBT, components of Dialectical Behaviour Therapy (DBT), Problem Solving Treatment (PST), and Mindfulness Based Cognitive Therapy (MBCT) are used in several exercises. DBT is a treatment program developed for borderline personality disorder and has been proven effective in reducing suicidal behaviour [20,22]. PST focuses on improving interpersonal problem solving skills and can be used for the treatment of a variety of mental disorders. It has shown promising results with regard to the treatment of suicidal thoughts [24,33]. MBCT was developed to prevent relapse and recurrence of depression [34], but may also be helpful in the treatment of suicidal thoughts [35]. It combines mindfulness meditation with cognitive therapy.

CBT, DBT, PST and MBCT are all rooted in cognitive therapy [36]. The underlying cognitive model states that emotion and behaviour are influenced by the way events or situations are interpreted. Dysfunctional cognitions can underlie these interpretations and contribute to the development of mental disorders. The cognitive model was originally aimed at explaining psychological processes in depression, but has been expanded to other mental disorders. Although suicidal thoughts and behaviours are not classified as a separate mental disorder, they are related to many mental disorders [37]. Dysfunctional thoughts seen in suicidal individuals often involve hopelessness, helplessness and unlovability [38]. Cognitive therapy techniques aim at restructuring such dysfunctional cognitions. In addition the ruminative, repetitive style of thinking often experienced by suicidal persons can be addressed with cognitive techniques [39-41].

#### Structure

The intervention consists of six modules, each of which can be completed in one week. A module starts by providing information, followed by an assignment and several exercises. Subjects are strongly advised to complete those. In addition, each module contains a number of optional exercises from which the subject can choose the ones that appeal to him. Finally, each module is provided with a number of 'Frequently Asked Questions'. Here, subjects can also actively pose questions which will be answered on a general, non personal level. Consequently no personal feedback or support by a therapist will be offered.

Ideally subjects need to spend at least 15 minutes twice a day to perform the exercises. Every week, an automated e-mail is sent as a reminder of the new module and as motivation to complete it.

#### Content of the modules

- Module 1 aims at teaching subjects to gain more control over their suicidal thoughts. The worrisome, repetitive aspects of suicidal thinking are outlined, and the exercises are aimed at reducing worry.

- Module 2 teaches subjects to recognize and prevent an upcoming crisis. An important message is that seemingly unbearable thoughts can be tolerated. Main goal is that subjects learn to tolerate and regulate intense emotions in a crisis situation.

- Module 3 explains the 'ABC model' which states that emotions (Consequences) are caused by a persons Belief about an Activating event (the trigger). Exercises focus on identifying automatic thoughts.

- Module 4 describes common distortions in thinking. Exercises deal with recognizing and changing them.

- Module 5 is about challenging negative thoughts by evaluating evidence for and against the validity. Exercises also focus on formulating thoughts in a more detailed and neutral way.

- Module 6 explains the possibility of relapse. Also, attention is given to the picture of the future and possible future setbacks. Exercises focus on making a relapse prevention plan and on formulating a more realistic picture of the future.

#### Waiting list control condition

Subjects in the control condition can access a website where information on suicidality is provided. The information is meant to inform them about the nature and possible causes of their thoughts and feelings. Discussed themes are prevalence, risk factors and warning signs. Also, information about treatment in general is provided, as well as links to several mental health organisations. After six weeks, subjects are provided with a login code for the intervention.

### Instruments

Due to the self-help character of this study, all measures are self-reports. No diagnostic instrument is administered.

#### Primary outcome measure

The primary outcome measure in this study is the reduction in frequency and intensity of suicidal thoughts, which is measured by the Beck Scale for Suicide Ideation.

##### Suicidal thoughts

The *Beck Scale for Suicide Ideation*, *self report *(BSS) [42] is a 21-item instrument to detect and measure the severity of suicide ideation. The BSS parallels the *Scale for Suicide Ideation *(SSI), which is a semi-structured interview [43]. Each item is scored from 0 to 2. The first five items of the BSS serve to screen for suicide ideation. If the subject selects zero for both item 4 and 5, he or she is instructed to go to item 20. Otherwise, all items are filled out. The last two items (20 and 21) assess the number of suicide attempts and the intent to die during the last attempt. The total score is obtained by adding the first 19 items, and ranges from 0 to 38. A higher score indicates more severe suicide ideation. The BSS has high internal reliability with Cronbach alpha ranging from 0.87 to 0.97, and moderate test-retest reliability (r = 0.54). The concurrent validity is high with the SSI (0.90 - 0.94), and moderate with the BDI suicide item (0.58 - 0.62).

#### Secondary outcome measures

Secondary outcome measures include depressive symptoms, hopelessness, anxiety symptoms, worrying, quality of life and costs related to health care utilization and production loss.

##### Depressive symptoms

The *Beck Depression Inventory Second Edition *(BDI-II) measures the severity of a depression, and is used to detect the presence of depressive symptoms [31,44]. This questionnaire was introduced in 1961 and is one of the most frequently used and validated instruments to assess depressive symptoms. The total score ranges from 0 to 63 and is obtained by adding the 21 items, which are rated on a 4 point scale (0-3). A higher score indicates more severe depressive symptoms. Interpreting the scores, a total score between 0 and 13 corresponds with minimal depression, 14-19 with mild depression, 20-28 with moderate depression, and 29-63 with severe depression. In both American and Dutch samples, good convergent validity and internal consistency were demonstrated [44].

##### Hopelessness

The *Beck Hopelessness Scale *(BHS) assesses hopelessness [45]. The BHS contains 20 'true-false' statements. Each statement is scored 0 or 1, resulting in a total score range of 0 to 20. A higher score indicates more hopelessness. The BHS is one of the most frequently used measures of hopelessness, and has excellent internal consistency and test-retest reliability. In addition, several studies have supported the predictive validity of the BHS for suicide attempts and suicide [46].

##### Anxiety symptoms

The anxiety subscale of the *Hospital Anxiety and Depression Scale *(HADS-A) is used to assess anxiety symptoms [47]. This subscale consists of 7 items, rated on a 4 point scale (0-3). Total score therefore ranges from 0 to 21, with higher scores indicating more anxiety symptoms. In several normal and clinical Dutch samples, homogeneity and test-retest reliability were good, with Cronbach alpha ranging from 0.80 to 0.84 [48].

##### Worrying

The *Penn State Worry Questionnaire *(PSWQ) was developed in 1990 to measure excessive and uncontrollable worrying [49]. Subsequently, an adapted version was published, which assesses pathological worry in the past week (PSWQ-PW) [50]. The PSWQ-PW is a 15 item self-report inventory with a 7 point rating scale, ranging from 'never' (0) to 'almost always' (6). The total score ranges from 0 to 90, with a higher score indicating more worrying. The PSWQ-PW shows good reliability and substantial convergent validity. It assesses both weekly status of worry and treatment-related changes of worry during treatment, which makes it suitable for monitoring pathological worry in research settings [50].

##### Quality of life

The *EuroQol *(EQ-5D) [51] is a standardised non disease specific instrument for describing and valuing health related quality of life. It consists of five items (mobility, self-care, usual activities, pain/discomfort and anxiety/depression). Each item is rated as 'no problem' (1), 'some problem' (2), or 'extreme problem' (3). The resulting health state can therefore be expressed by a five-digit number. In addition, it is required to rate current health state on a thermometer ranging from 0 (worst imaginable health state) to 100 (best imaginable health state).

##### Costs: health care utilization and production loss

Health care utilization and production loss are evaluated by means of the *Trimbos/iMTA questionnaire for Costs associated with Psychiatric Illness *(TiC-P) [52]. The TiC-P consists of two different parts that can be administered separately. Part I is concerned with measuring the direct costs of care consumption of subjects with psychiatric disorders. It consists of 15 items, but can be customized for the study population. Items that are considered irrelevant can be left out. Part II is meant to determine indirect costs resulting from production loss associated with psychiatric disorders. It consists of the *Short Form Health and Labor Questionnaire *(SF-HLQ) [53]. The SF-HLQ contains three modules covering absence from paid employment, production loss without absence from paid employment and impediments to paid of unpaid employment.

##### Functioning

The *Work and Social Adjustment Scale *(WSAS) [54] measures impaired functioning attributable to an identified problem. It is a five item scale, with each item being rated on a 0 (no impairment at all) to 8 (very severe impairment) scale. The WSAS is valid and reliable. Internal consistency ranges from 0.70 to 0.94. Test-retest correlation was 0.73.

### Statistical analyses

To test the hypothesis that the self-help intervention is superior to the control condition, the analysis will be conducted on an Intention to Treat basis following the pertinent BMJ & Consort guidelines. Missing observations at follow up will be imputed by regression imputation or multiple imputations, stratified for predictors of outcome and loss to follow-up. Relative improvements in frequency and intensity of suicidal thoughts in the experimental group in comparison with the control group will be calculated by Cohen's *d*. For this confirmatory analysis the primary outcome measure is used (BSS). To the exploratory analyses of the secondary outcome measures, a Bonferroni correction will be applied to control the overall Type I error rate.

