**Methods/Design:**

In this study, a recently developed self-help intervention will be evaluated in a Randomized Controlled Trial. The intervention is based on Cognitive Behavioural Therapy and is aimed at subjects who experience mild to moderate suicidal thoughts. This is defined as a score between 1 and 26 on the Beck Scale for Suicidal Ideation (BSS). Higher and lower scores are excluded. In addition, severely depressed subjects are excluded. In total, 260 subjects will be randomly allocated to the intervention-condition (N = 130) or to the information-control condition (N = 130). Self-report questionnaires will be filled out at baseline, 6 weeks after baseline and 18 weeks after baseline. Primary outcome measure is the reduction in frequency and intensity of suicidal thoughts. Secondary outcome measures are the reduction of hopelessness, anxiety and depression, sleeplessness, worry and quality of life measures.

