### Sample size

The sample size of this study is based on the expected effect on the primary outcome measure, i.e. the reduction in frequency and intensity of suicidal thoughts. In order to be able to demonstrate a clinically relevant effect-size of 0.35 with α = 0.05 and β = 0.80, 100 subjects are needed in each condition. When including an expected drop-out of 30%, the total sample size is determined at 260. The effect-size of 0.35 is based on effect-sizes found in other studies into internet interventions, mainly for depression [28,29].

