### Safety of subjects

Since this study will be conducted in a vulnerable population in which suicide may occur, a safety protocol has been developed. In addition to the pre-, post and follow-up measures, suicidal thoughts will be assessed bi-weekly in both the experimental and the control condition during the first six weeks by means of the BSS and the BDI. The safety protocol will be applied when a subject exceeds the determined cut-off scores, i.e. BSS ≥ 27 or BDI ≥ 40. When this occurs, the researchers will contact the subject by phone on the same day the score is received to assess the suicide risk and contact the GP if necessary. If the phone is not answered, calling will be continued for two days on different times of the day. In case of no response after two days, a standardized e-mail expressing worry will be sent. In this e-mail, it will also be requested to contact the researchers. In addition, it will be explained that the GP will be contacted three days after sending this e-mail. If the GP is not reached, the locum GP is contacted. In case a subject drops out of the study, i.e. does not fill in the questionnaires, an e-mail will be sent with the request to reply and the explanation that the GP will be contacted in case of no reply within three days.

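### The plan permits single regression imputation with 30% dropout expected; this can inflate type I error or, if arm is left out of the imputation model, dilute the effect

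*Protocol article*

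**What the plan says.** Statistical analyses promises an intention-to-treat analysis and states: "Missing observations at follow up will be imputed by regression imputation or multiple imputations", "stratified for predictors of outcome and loss to follow-up". The same paragraph expresses the effect as Cohen's d and names the BSS as the outcome for the confirmatory analysis, so the imputation rule bears on the primary result.

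The article does not say:
- which of the two methods will be used;
- whether regression imputation adds a random residual;
- whether arm is in the imputation model;
- how the standard error allows for imputed values;
- which test will be applied.

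The Sample size section shows how much could be missing: "When including an expected drop-out of 30%, the total sample size is determined at 260".

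**The concern.** The two methods are presented as interchangeable, but they are not. Multiple imputation with Rubin's rules adds the between-imputation variance to the standard error. Single regression imputation, followed by an ordinary analysis of the completed data, treats each predicted value as a measurement. It counts 260 outcomes when about 0.30 x 260 = 78 of them may be model output.

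At stake is either the 5% level of the confirmatory BSS test and the width of its confidence interval, or the size of the estimated effect. Which one depends on a detail that the article leaves open.

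**Working it through.** **Inputs from the article.** Sample size: "effect-size of 0.35 with α = 0.05 and β = 0.80" (0.80 is taken as power), "100 subjects are needed in each condition", 30% dropout, total 260. Abstract: 130 per arm.

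**Assumed inputs.** The baseline-outcome correlation r is not given. The BSS test-retest value of 0.54 in the Instruments section serves as an anchor, with range 0.3-0.7. The test is also assumed: ANCOVA, a t-test on the follow-up score, or a t-test on change.

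**The plan's own figure.** n per arm = 2(z_α + z_power)²/d².
- One-sided: 2(1.645 + 0.842)²/0.35² = 100.9, so 101. This matches the stated 100.
- Two-sided: 2(1.960 + 0.842)²/0.35² = 128.1, so 129. This does not match.
- Dropout: 200 x 1.3 = 260, so the enrolment leaves room for 60/260 = 23% loss. Both 23% and 30% missing were therefore examined.

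**Large-sample formula: ANCOVA, arm in the imputation model, missing share m.** Take the variance of the effect with full data as 1.
- *Deterministic fill-in.* The estimate carries only complete-case information, so its true variance is 1/(1-m). Imputed residuals are zero, so the reported variance is about (1-m). The reported SE is (1-m) times the true SE, and the effective critical value is 1.96(1-m). At m = 0.30: 1.96 x 0.7 = 1.37, two-sided type I error 0.170.
- *Stochastic fill-in (one random residual).* True variance is 1/(1-m) + m and reported variance is about 1. At m = 0.30: 1/0.7 + 0.3 = 1.729, square root 1.315, critical value 1.96/1.315 = 1.49, type I error 0.136.

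Confidence intervals are therefore about 70% (deterministic) or 1/1.315 = 76% (stochastic) of the width they should have.

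**Simulation.** 130 per arm, no true effect, 30% missing completely at random, arm in the imputation model; 5000 runs per setting (3000 for multiple imputation). Two-sided type I error at nominal 0.05:

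| Method and test | r = 0.3 | r = 0.54 | r = 0.7 |
|---|---|---|---|
| Deterministic, ANCOVA | 0.170 | 0.179 | 0.175 |
| Deterministic, t-test on follow-up score | 0.154 | 0.131 | 0.099 |
| Deterministic, t-test on change | 0.119 | 0.136 | 0.146 |
| Stochastic, ANCOVA | 0.125 | 0.137 | 0.134 |
| Stochastic, t-test on follow-up score | 0.117 | 0.116 | 0.089 |
| Stochastic, t-test on change | 0.101 | 0.116 | 0.122 |
| Multiple imputation (20, Rubin's rules) | 0.044 | 0.053 | 0.049 |

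Other settings:
- Missing at random instead of completely at random (deterministic, ANCOVA): 0.174.
- 23% missing: ANCOVA about 0.135 deterministic and 0.106-0.120 stochastic; t-tests about 0.08-0.12.
- One-sided nominal 0.05, ANCOVA, 30% missing: about 0.125 deterministic and 0.10 stochastic.

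**Arm left out of the imputation model, 30% missing.** Type I error is 0.047-0.056 in every setting, so there is no inflation. Imputed subjects carry no arm difference, so the expected raw difference is (1 - 0.30) x 0.35 = 0.245 in baseline-SD units.

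**The case against.** **The size is conditional.** A reader might infer that single imputation always more than doubles the type I error. The article does not support that. It names no test, and the inflation requires arm to be in the imputation model. With a t-test on the follow-up score at r = 0.7 the error is slightly under double (0.089-0.099), and some settings at 23% missing are also below double. Even 30% missing at the confirmatory comparison is an assumption, because dropout is given only as one overall figure. This objection stands.

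**The two harms exclude each other.** Inflation needs arm in the model and dilution needs it out. A reader might add them together; that would be wrong.

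**Silence about arm is not exclusion.** The phrase "stratified for predictors of outcome and loss to follow-up" neither lists variables nor rules arm out, and a journal article commonly leaves the covariate list to a fuller document. It cannot be said that the plan omits arm.

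**The same holds for the interim scores.** The Safety section says "suicidal thoughts will be assessed bi-weekly in both the experimental and the control condition during the first six weeks", and nothing says these scores will be kept out of the imputation. Using them is optional, with a variance gain of perhaps 3-8% under assumed correlations.

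**The choice may be fixed elsewhere.** An analysis plan that is not shown may settle the method before the data are seen, so a choice made after the results is a possibility and not a fact.

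What remains is that the article itself approves single regression imputation as an alternative and states no variance correction. That is a stated choice and not merely an omitted detail.

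**Conclusion.** The point holds in conditional form. Anyone who follows the first permitted option and analyses the completed data as observed gets a flawed primary result either way. With arm in the imputation model and 30% missing, the two-sided error rate is about 0.13-0.18 (ANCOVA) or 0.09-0.15 (t-test on the follow-up score) in place of 0.05, with intervals that are too narrow. Without arm, the level holds but the effect falls to about 70% of its true value.

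The direction of the first harm follows from the formulas. Its size rests on r between 0.3 and 0.7, on the assumed test and on 30% missing at the comparison. Multiple imputation with arm in the model brings the error rate back to 0.044-0.053.

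**What to change.** In Statistical analyses, strike the regression-imputation option and name one primary method in advance: multiple imputation with Rubin's rules and randomised arm in the imputation model. Arm must be named because leaving it out would dilute the effect under multiple imputation too. A likelihood-based repeated-measures model is a comparable alternative but not identical, since the two can condition on different variables; choose one.

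The bi-weekly BSS and BDI scores may be added as auxiliary variables if wanted.

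The cost is a change of wording and slightly more programming, with no new data. Confidence intervals will be wider than under single imputation because they then reflect the information lost to dropout.

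### The plan leaves single regression imputation open for the confirmatory BSS comparison; with arm in the imputation model and 23–30% of scores missing, type I error could rise from 5% to roughly 10–17%

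*Protocol article*

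**What the plan says.** The Statistical analyses section sets an intention-to-treat test of superiority and deals with missing outcomes in one sentence: "Missing observations at follow up will be imputed by regression imputation or multiple imputations, stratified for predictors of outcome and loss to follow-up". It does not choose between the two methods and mentions no variance correction for the first. The same section makes the BSS the confirmatory outcome and names the effect measure: "Relative improvements in frequency and intensity of suicidal thoughts in the experimental group in comparison with the control group will be calculated by Cohen's" *d*.

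The Sample size section shows how much imputation to expect: "When including an expected drop-out of 30%, the total sample size is determined at 260". Of 260 randomised subjects, 30% is 78. If the allowance is read as 130 recruited for 100 needed, it is 30/130 = 23% per arm, or 60 subjects.

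The article gives no correlation between baseline and follow-up BSS. The nearest figure, under Suicidal thoughts, is "moderate test-retest reliability (r = 0.54".

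**The concern.** The two methods are not interchangeable for inference. Multiple imputation carries the uncertainty about each imputed value into the standard error. Single regression imputation does not: the completed file of 260 is analysed as though every score had been observed, and the standard error comes out too small. Choosing good predictors of outcome and drop-out improves the predictions but does not remove this.

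The effect measure is exposed as well. Cohen's *d* has the standard deviation in its denominator, and deterministic imputation places values on the regression line and so shrinks that standard deviation. If the regression omits treatment arm, the imputed values instead pull the two arms together.

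At stake is the confirmatory result: its false-positive rate, the coverage of its confidence interval, and the size of the reported effect.

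**Working it through.** **The plan's own figures.** The article states no error rate under imputation, so the only planned value to compare with is α = 0.05. The sample size is stated as: "effect-size of 0.35 with α = 0.05 and β = 0.80, 100 subjects are needed in each condition". Reading β as power, 2(1.645 + 0.842)²/0.35² ≈ 101 per arm, so 100 is reproduced with a one-sided α; the two-sided figure is 129. The total follows as 2 × 100 × 1.30 = 260. This matters here only because it gives two readings of the missing fraction, 23% and 30%. The results below use a two-sided 5% test.

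**Inputs.** From the article: n = 130 per arm and m = 0.30 missing (also 0.23). Assumed: scores missing completely at random, standard deviation 1, and baseline–outcome correlation r = 0.54 (the test–retest value used as a proxy, varied below). Write o = 1 − m.

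**Deterministic imputation from baseline BSS and arm, final-score t-test.**
- True variance of an arm mean: (1 − r²)/(on) + r²/n = 0.7084/91 + 0.2916/130 = 0.01003.
- Variance the usual test assumes: (o + m r²)/n = 0.7875/130 = 0.00606.
- Actual type I error: 2[1 − Φ(1.96 √(0.00606/0.01003))] = 12.8%, so a 95% interval covers about 87%.
- Inflation of *d*: 1/√0.7875 = 1.127.

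**Change score.** True variance 0.7084/91 + 0.46²/130 = 0.00941. Assumed variance (0.7 × 0.92 + 0.3 × 0.2116)/130 = 0.00544. Type I error 13.6%.

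**Baseline-adjusted model (ANCOVA).** The variance ratio is o² = 0.49, so type I error is 2[1 − Φ(1.96 × 0.7)] = 17.0%.

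**Arm left out of the regression.** Both arms share one fitted line, so under the null the imputed part cancels from the difference. The true variance becomes [r² + o(1 − r²)]/n, which equals the assumed (o + m r²)/n, and type I error stays at 5%. A true difference of 0.35, however, shrinks to about 0.7 × 0.35 = 0.245.

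**Simulation at r = 0.54, 30% missing, 130 per arm.** Type I error used 20,000 runs per scenario and *d* 8,000 runs, except the fourth row (6,000 runs, final score only) and the last (20 imputations, 3,000 runs).

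| Imputation | Type I: final score | Type I: change | Type I: ANCOVA | *d* when true *d* = 0.35 (final score) |
|---|---|---|---|---|
| Deterministic, arm in | 12.6% | 13.6% | 17.3% | 0.40 |
| One random residual, arm in | 10.9% | 11.4% | 13.8% | 0.35 |
| Deterministic, arm out | 5.1% | 5.1% | 5.0% | 0.28 |
| One random residual, arm out | 5.4% | – | – | 0.24 |
| Multiple imputation, Rubin's rules, arm in | 4.6% | – | 5.3% | – |

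**Sensitivity (deterministic, arm in).**
- r from 0.3 to 0.7 at 30% missing: about 16% down to 10% for the final score, and 12% up to 15% for the change score.
- 23% missing at r = 0.54: 10.4% for the final score (10.5% simulated), 10.9% for the change score and 13.2% for ANCOVA; *d* is inflated by 9%.
- Stronger predictors at 30% missing, replacing r² by an assumed model R² in the final-score formula: R² = 0.5 gives 10.1% with *d* up 8.5%; R² = 0.6 gives 8.9% with *d* up 6.6%.

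**The case against.** A reader might infer that the plan as written raises the false-positive rate to 13% and overstates Cohen's *d*. The article does not support that as an unconditional statement. It does not say whether a residual is added, whether arm is in the imputation model, or whether the test uses final scores, change scores or a baseline-adjusted model. With a residual, *d* is not inflated. With arm omitted, type I error stays near 5% and *d* is biased towards zero. If the trial uses multiple imputation, which the same sentence allows, the problem does not arise.

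The imputation model may also be stronger than baseline BSS alone. The sentence refers to predictors in the plural, and the Safety of subjects section adds bi-weekly BSS and BDI in both arms during the first six weeks. This lowers the inflation, on the R² values assumed above, to about 9–10%, but does not remove it. The 23% reading of the drop-out allowance likewise lowers the figure without removing it.

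A reader might also infer that the method could be picked after both results are seen. That cannot be established: this is a condensed article, and a statistical analysis plan that is not shown may settle the choice.

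What these objections do not answer is that the article names, for its confirmatory outcome, a method that misleads when applied in the usual way. That is a stated option, not a detail left for later. All four basic versions of it checked here fail in one direction or the other: either the test is anti-conservative or the effect is attenuated.

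**Conclusion.** The point holds in conditional form. Single regression imputation is permitted on equal terms with multiple imputation for the confirmatory BSS comparison, with 30% drop-out expected. If it is used with arm in the model and the completed data are analysed as observed, the two-sided type I error could rise from 5% to roughly 10–17%; about 13% applies to deterministic imputation with 30% missing and r = 0.54. The direction of the error in *d* depends on choices the article does not state: about 13% too large, roughly unbiased, or about 20–30% too small.

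These sizes rest on data missing completely at random, equal missingness in the arms, and a correlation borrowed from test–retest reliability. That the standard error is understated when arm is in the model does not depend on the exact value of r: it appears at every value tried.

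**What to change.** In the Statistical analyses section, delete the words *regression imputation or*. State that missing BSS values will be multiply imputed with treatment arm in the imputation model (or separately by arm), that the treatment difference will be estimated in each completed data set, and that estimates and standard errors will be combined by Rubin's rules. State that Cohen's *d* will be computed from the pooled difference and a properly pooled or observed-data standard deviation, not from a singly imputed file. The number of imputations and the imputation algorithm are matters of preference; 20 imputations were enough in the simulation above.

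The cost is one sentence of wording, slightly more computing, and a confidence interval that is wider because it reflects the missing data honestly. The design and the recruitment target do not change on this account.

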### Randomization

Subjects will be randomized in blocks of 20 after stratification for gender. An independent researcher makes the allocation schedule using random allocation software. Subjects will be informed about the randomization outcome by means of an e-mail, which will also contain a login code for the assigned condition.

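### The confirmatory analysis is fixed only as a Cohen's d of BSS improvement; modelling 6-week BSS on arm, baseline BSS and gender would be more precise at no data cost

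*Protocol article*

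**What the plan says.** The protocol article defines the primary outcome as a reduction in suicidal thoughts on the BSS (Primary outcome measure). The Statistical analyses section opens with a testing aim, "To test the hypothesis that the self-help intervention is superior to the control condition", and then gives the method: "Relative improvements in frequency and intensity of suicidal thoughts in the experimental group in comparison with the control group will be calculated by" Cohen's d. It labels this the confirmatory analysis. The section also covers the intention-to-treat principle, imputation and a Bonferroni correction for secondary outcomes. It names no test, model or covariate.

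On the design side, "Subjects will be randomized in blocks of 20 after stratification for gender" (Randomization). Gender does not reappear in the analysis section. Baseline BSS is not a stratification factor, and eligible scores run from 1 to 26.

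The only figure for agreement between two BSS measurements is in the instrument description: "moderate test-retest reliability (r = 0.54". Neither the interval nor the population is given.

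**The concern.** A reduction compared between arms is, on its natural reading, a comparison of change from baseline. That is valid under randomisation but is rarely the efficient choice. Subtracting the whole baseline score over-corrects unless the correlation is close to 1, so noise is added back. It also leaves chance baseline imbalance in the estimate: an arm that happens to start higher will appear to improve more, through regression to the mean. With one stratification factor and a wide eligible BSS range, nothing in the design prevents such an imbalance.

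At stake are the precision of the main result and its robustness to an accident of allocation. Both can be improved with data the trial already collects.

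**Working it through.** **Inputs.** From Sample size: "effect-size of 0.35 with α = 0.05 and β = 0.80" (the 0.80 read as power), "100 subjects are needed in each condition", and "When including an expected drop-out of 30%, the total sample size is determined at 260". Allocation is 130 to 130 (Abstract). Completers per arm: 130 × 0.70 = 91. Sidedness is not stated, nor is whether d = 0.35 is scaled to the SD of the final score or of the change. The baseline-to-week-6 correlation r is not given; 0.54 is borrowed from the test-retest figure, and a range is shown.

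**The plan's own figure.** n per arm = 2 × [(z₁₋α + z₀.₈₀)/d]².
- One-sided: 2 × (1.645 + 0.842)²/0.35² = 100.9, which matches the stated 100 to rounding.
- Two-sided: 2 × (1.960 + 0.842)²/0.35² = 128.1, which does not.

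Both versions are therefore carried forward.

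**Variances**, relative to a comparison of final scores, with equal SDs at both times:
- change score: 2(1 − r); at r = 0.54, 0.92
- covariance adjustment (ANCOVA): 1 − r²; at r = 0.54, 0.708
- ratio of ANCOVA to change: (1 + r)/2; at r = 0.54, 0.77

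The last ratio is below 1 for every r below 1, so the direction does not depend on the assumed value.

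**Power.** Two-sample t-test (noncentral t), α = 0.05, 91 per arm, with d divided by the square root of the variance ratio. The one degree of freedom spent on the covariate is ignored. For d on the final-score SD at r = 0.54, the effective d is 0.35/√0.92 = 0.365 for change and 0.35/√0.708 = 0.416 for ANCOVA.

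| r | Two-sided: change | ANCOVA | Gain (points) | One-sided: change | ANCOVA | Gain (points) |
|---|---|---|---|---|---|---|
| 0.3 | 0.510 | 0.692 | 18 | 0.634 | 0.794 | 16 |
| 0.4 | 0.573 | 0.727 | 15 | 0.692 | 0.822 | 13 |
| 0.54 | 0.687 | 0.797 | 11 | 0.790 | 0.875 | 8 |
| 0.7 | 0.858 | 0.908 | 5 | 0.918 | 0.950 | 3 |
| 0.8 | 0.960 | 0.975 | 1 | 0.981 | 0.989 | 1 |

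If d = 0.35 is instead on the change-score SD, the change analysis has power 0.651 two-sided or 0.760 one-sided at any r. ANCOVA then has an effective d of 0.35/√0.77 = 0.399 at r = 0.54, giving 0.763 two-sided or 0.850 one-sided: gains of 11 and 9 points. On this scale the two-sided gain runs from 18 points at r = 0.3 to 5 at r = 0.8. The normal approximation gives the same picture, within about half a point.

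**Baseline imbalance.** If the intervention arm starts Δ points higher by chance, the change-score difference carries an expected error of (1 − r)Δ in its favour. At r = 0.54 and Δ = 1 BSS point, that is 0.46 points. Covariance adjustment removes it under the linear model.

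**Gender.** The document gives no association between gender and BSS, so no effect on power can be computed.

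**The case against.** The strongest reply is that this is one paragraph of a journal article. It does not say the comparison is unadjusted, it excludes no covariate, and a Cohen's d can be taken from an adjusted model. Model form is commonly left to a full protocol or analysis plan, which is not shown. This stands as a limit on the claim: the lack of adjustment is inferred. But the outcome definition and the one named statistic both point to change scores, so the text steers towards the less efficient method.

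Several stronger readings are tempting and are not supported:
- *That the plan ignores baseline BSS.* An improvement already subtracts the baseline; it is used inefficiently.
- *That about 15 points of power are lost.* That figure compares ANCOVA with an analysis of week-6 scores alone (0.651 against 0.797 two-sided), which the plan does not propose.
- *That 0.54 is the trial's own correlation.* It is a reliability figure, not a 6-week correlation in a treated sample restricted to BSS 1 to 26.
- *That leaving out gender invalidates the standard error.* Omitting a prognostic stratum from a linear analysis generally makes the standard error conservative.
- *That no test is intended.* The section speaks of testing a hypothesis; the test is simply not named.
- *That the change-score estimate is biased.* Over repeated randomisation it is not; the error from imbalance is conditional on the allocation obtained.

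**Conclusion.** The point holds as one of efficiency. The article fixes the confirmatory comparison as a Cohen's d of improvement and states no baseline or gender term. A covariance-adjusted model is more precise for every r below 1 under equal variances. At an assumed r = 0.54 with 91 completers per arm, the gain is about 11 points of power two-sided and 8 to 9 one-sided, whichever SD d is scaled to. Over r from 0.3 to 0.8, the two-sided gain runs from 18 points down to 1 (d on the final-score SD) or 5 (d on the change SD). The direction is firm and the size is conditional. Whether the sample size itself is adequate is a separate question on which this point does not rely.

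**What to change.** State the primary analysis as a linear model of 6-week BSS on arm, baseline BSS (continuous) and gender. Six weeks is the last assessment before controls receive the intervention. Report the adjusted difference with its 95% CI and p-value, and state whether the test is one- or two-sided. Keep Cohen's d as a descriptive effect size: the adjusted difference divided by one SD named in advance, such as the pooled baseline SD. Use the same form for each continuous secondary outcome with its own baseline. If a power gain is quoted, give the assumed correlation with it.

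The cost is a change of wording. Baseline questionnaires are completed before randomisation, and gender must be known to randomise, so no extra data or subjects are needed.
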